**Results:**

Community engagement has commenced, and data collection protocols have been prepared. Staff specific to the study (eg, Aboriginal health practitioners or workers) are in the process of recruitment. Participant recruitment will commence in March 2026 and conclude in December 2026. Study outcomes will be reported at 12- and 24-month follow-ups.

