### Outcomes

The primary outcome of interest is the number of treated decayed teeth at baseline that became arrested at each follow-up period and the number of sound surfaces treated at baseline that became carious at follow-ups, measured by the count of decayed, missing, and filled tooth surfaces. Secondary outcomes will be changes in COHRQoL and child dental anxiety (Table 1).

**Table 1 table1:** Standard Protocol Items: Recommendations for Interventional Trials (SPIRIT) participant timeline.

SPIRIT participant timeline		Enrollment	Allocation	After allocation			Closeout
		–T1^a^		Baseline	12 mo	24 mo	

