### Sample Size

We used the *power* command within Stata (version 15; StataCorp) and data on decay incidence, restorative outcomes, and COHRQoL impacts from the recently completed Kimberley study [6] to estimate the noninferiority sample size. Approximately 61% of the ART restorations were classified as successful (lesion arrestment), and 81% were estimated to be arrested with AgF treatment from published studies [19]; community intracluster correlation was 0.09. Using these parameters at 80% power and an α of .05 and with 30 clusters available (n=15, 50% clusters per treatment arm), the estimated sample size required was 180 in each arm. Allowing for a 25% loss to follow-up each year, the estimated sample size is 320 per arm or 22 children per cluster (rounded up). The sample size will also have 84% power to undertake subgroup analyses to detect a 20% difference in caries arrestment between carious lesions treated with AgF and KI or without KI. A sample size of 40 for the focus group interviews is expected to be sufficient to allow for the elicitation of parent perceptions about the care provided based on our earlier work [20,21].

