### Data Collection and Management

#### Plans for Assessment and Collection of Outcomes

Treated teeth with intact, sound fillings will be assumed to have arrested decay. The changes will be evaluated through a count of decayed, missing, filled, and arrested decayed tooth surfaces at baseline and 12- and 24-month follow-ups using the International Caries Detection and Assessment System criteria [22]. The assessment will be undertaken by calibrated examiners. Color changes of AgF-treated or AgF- and KI-treated lesions will be evaluated through the classification of the treated lesion into 4 categories according to Pantone color plates. Data will be collected through direct data entry using the REDCap (Research Electronic Data Capture; Vanderbilt University) implementation on iPads (Apple, Inc). The Aboriginal research assistant will assist parents, carers, and children whose primary language is not English in completing the questionnaire.

Parents of the study participants will be invited to take part in focus group interviews at the 12-month follow-up. Consenting parents will be interviewed by the Aboriginal research assistant using a semistructured interview schedule, and the interviews will be digitally recorded. The structured open-ended questions will elicit responses from parents on the care received by their child and follow a yarning approach [12]. The questions will be based on the following:

What were some of the positive aspects of dental care experienced by your child?What were some of the negative aspects of the dental care received by your child?Can you give some examples of what you think could have been done and implemented better during your child’s treatment?Can you name some aspects of the setting, location, and process that you think could have been improved?Can you identify any changes to your oral health knowledge since the research began?

We will also take digital images of the teeth of selected children who provide consent to have the images of their teeth recorded using a smartphone and a standardized protocol [15]. The images will be sent via email, using a secure protocol used within the Western Australia Health Department, to a remote site where an independent, calibrated assessor will assign scores to the images using the same criteria as the field assessment.

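### The primary outcome is two outcomes of different hypothesis type, each at 12 and 24 months, with none named as deciding, while the sample size covers only caries arrest

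*Protocol article*

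**What the plan says.** The Outcomes section names as the primary outcome the number of treated decayed teeth "that became arrested at each follow-up period and the number of sound surfaces treated at baseline that became carious at follow-ups", the two parts joined by 'and'. Assessment takes place "at baseline and 12- and 24-month follow-ups using the International Caries Detection and Assessment System criteria" (Plans for Assessment and Collection of Outcomes), so the follow-ups are at 12 and 24 months. Quality of life and dental anxiety are the secondary outcomes.

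The Objectives section attaches different hypotheses to the two parts. Objective 1 expects more arrested lesions in the intervention group, which is superiority wording. Objective 2 expects new decay to be no worse than a specified risk difference, which is noninferiority wording, and gives no number. Trial Design labels the whole study a noninferiority trial. Statistical Methods sends objectives 1 to 3 to the same set of methods without ranking them.

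The Sample Size section starts from "Approximately 61% of the ART restorations were classified as successful (lesion arrestment") against an assumed 81% with silver fluoride (AgF) and an intracluster correlation of 0.09. It continues: "Using these parameters at 80% power and an α of .05 and with 30 clusters available (n=15, 50% clusters per treatment arm"), arriving at 180 per arm. "Allowing for a 25% loss to follow-up each year", this becomes 320 per arm. On reporting, the abstract says: "Study outcomes will be reported at 12- and 24-month follow-ups".

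**The concern.** Arrest and new caries at two visits make four outcome-by-time results, all under the label of primary outcome. They cannot be read as one test. One part counts teeth and the other surfaces; one is worded as superiority and the other as noninferiority. AgF is reapplied at 12 months, so the two visits also assess different amounts of treatment.

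Two things are at stake. First, a trial in which arrest succeeds and prevention fails, or in which 12 and 24 months disagree, has no defined primary answer. Second, neither obvious rule preserves the stated operating characteristics. If any one result suffices, the error rate rises above its nominal level. If all must succeed, the stated power does not describe the trial.

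**Working it through.** **Inputs.** Arrest rates 0.61 and 0.81; α .05 (sidedness not stated); power 80%; K = 15 clusters per arm; intracluster correlation ρ = 0.09; 25% loss per year. All are from the Sample Size section.

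**1. Reproduce the plan's figure from arrest alone.**
- Unclustered, two-sided .05, mean rate 0.71: n = [1.960·√(2·0.71·0.29) + 0.842·√(0.61·0.39 + 0.81·0.19)]² / 0.20² = 79.6.
- With continuity correction: (n/4)·[1 + √(1 + 4/(n·0.20))]² = 89.3, so 90 per arm.
- Children per cluster: m = n(1−ρ)/(K − nρ) = 90·0.91/(15 − 8.1) = 81.9/6.9 = 11.87, so 12.
- Per arm: 12 × 15 = 180, the stated figure.
- Two years of loss: 180/(0.75 × 0.75) = 320, the stated figure.

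Other settings at 80% power do not give 180: two-sided without the correction gives 150; one-sided .05 gives 105, or 120 with the correction.

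**2. What the calculation covers.** Both stated figures follow exactly from the arrest rates, and the inflation is for two years of loss, so the target is arrest at 24 months. The section says that decay-incidence data were used, but no incidence rate and no noninferiority margin enters. Arrest at 12 months is not sized separately. With one year of loss, 320 × 0.75 = 240 per arm remain (16 per cluster), and by the same method power would be about 86%. For new caries, power cannot be computed at either visit.

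**3. If any one of the four results may support a primary claim.**
- Favourable claims only, one-sided .025 each: 1 − 0.975⁴ = 9.6%, against a nominal 2.5%.
- Two-sided .05 each, independent: 1 − 0.95⁴ = 18.5%, against a nominal 5%.
- The documents give no correlations. Assuming 0.3 to 0.9 between visits and 0 to 0.5 between outcomes, simulation gives about 6.3% to 9.3% on the first count and 12.6% to 18.2% on the second.

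**4. If all must succeed.** The type I error is not inflated. Joint power cannot exceed the power of the weakest component. That component may be new caries, whose power is unknown, so no figure can be given.

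**5. Price of splitting α instead** (same method as step 1).

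| Rule | Unclustered per arm | Per cluster | Per arm | Per arm after loss | Power for arrest at 180 per arm |
|---|---|---|---|---|---|
| One primary, .05 | 90 | 12 | 180 | 320 | 81% |
| Bonferroni over 2, .025 | 107 | 19 | 285 | 507 | 72% |
| Bonferroni over 4, .0125 | 124 | 30 | 450 | 800 | 62% |

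**The case against.** The strongest reply is that testing order and α allocation are commonly left to a statistical analysis plan, that none is shown, and that a journal article condenses the protocol. That stands for the method of adjustment, and its absence is not the point here. It does not cover the choice of primary outcome and time point. That is a protocol decision, which the Outcomes section makes in the plural and the Sample Size section makes in the singular.

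The reply also rightly limits several stronger readings that a reader might infer:

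- *That all four results are to be tested at .05.* The only .05 is in the Sample Size section, for arrest. Statistical Methods assigns no level to any test.
- *That the trial has four chances of success.* The two parts are joined by 'and', and the protocol does not say whether either or both must succeed.
- *That the error rate is 18.5%.* This treats new caries as a two-sided difference test, whereas objective 2 makes it a one-directional noninferiority claim. It also counts results against AgF as false claims. It is an upper figure for one set of assumptions, and 9.6% is the corresponding figure for favourable claims.
- *That joint power is 0.80⁴ = 41%.* This gives new caries 80% power without a stated rate or margin. It also assumes that the same lesions seen twice are independent.
- *That a separate confirmatory claim at 12 months is planned.* The abstract only promises reporting at both follow-ups, and the main Results section can be read as publication after both are complete.

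Finally, making arrest the sole primary outcome sits awkwardly with the noninferiority label, because the clinical noninferiority hypothesis belongs to new decay. That is a fair point, and the fix has to deal with it.

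**Conclusion.** The point holds in this form: the primary outcome as written is four outcome-by-time results of two hypothesis types with no deciding one, and the sample size supports only arrest after two years of loss. The second part is firm, since 180 and 320 reproduce exactly from the arrest rates.

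The size of the error-rate problem depends on a rule that the protocol does not state. If any one result suffices, the rate is at most 9.6% for favourable claims at one-sided .025 and 18.5% for independent two-sided .05 tests. Under the assumed positive correlations it is lower on both counts but still above nominal. If all must succeed, the error rate is not inflated, but the stated 80% is no longer the power of the trial and the document does not allow the true figure to be worked out.

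**What to change.** - Name caries arrest at 24 months as the single primary outcome. This matches the existing calculation and leaves 180 and 320 per arm unchanged.
- Make new caries at 24 months the first key secondary outcome, tested only if arrest succeeds, against a noninferiority margin stated as a number. Note that the stated power does not cover it.
- Make both 12-month results secondary, reported with confidence intervals.
- Align the noninferiority label in Trial Design with this hierarchy.

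If the investigators prefer arrest and new caries as co-primary, they should say that both must succeed, fix the time point, and restate the power for each. That needs a caries-incidence rate and a margin, and it may change the sample size.

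The cost of the recommended route is mainly wording, plus the work of choosing and justifying the margin. Any other public description of the outcomes should be brought into line. Recruitment is planned from March 2026, so the change can be made before outcome data exist if it is made promptly. The real downside is that a favourable 12-month or prevention result alone can no longer be called the primary result.

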**Methods:**

This study is a cluster-randomized controlled trial with communities randomized and stratified based on caries level and water fluoridation status. The trial will recruit 640 children (aged between 6 months and 7 years) from 30 communities. Informed consent will be obtained. At baseline, each child in the intervention group will be examined by a calibrated examiner and subsequently by an oral health practitioner who will prescribe to an Aboriginal health practitioner the teeth to be treated with AgF. A formulation with 38% AgF will be applied for 1 minute (0.004 mL per tooth). The control group will be provided with standard minimally invasive care. Participants will be followed annually for 2 years to assess caries arrest and prevention by blinded calibrated examiners. Child oral health–related quality of life and dental anxiety will be elicited through validated questionnaires. Tests of proportions will be used to evaluate the proportion of lesions arrested and the proportion of surfaces at risk that decayed over the follow-up. Multiple logistic regression with appropriate control for clustering of teeth and communities will be used to evaluate caries arrest, controlling for potential confounding factors.

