**For Riva Star Aqua**
Remove food debris and plaque by brushing with a toothbrush (no toothpaste).Isolate teeth to be treated with cotton rolls and gauze and apply petroleum jelly to the gingiva and lips.Dry the affected tooth surfaces and at-risk tooth surfaces to be treated with cotton pledgets.Dispense 0.05 mL AgF; bend the microbrush applicator and dip the tip of the applicator into the agent.Apply the agent with the microbrush onto the decayed surface and rub gently, maintaining contact with the tooth for 60 seconds; apply the agent also to at-risk, non-decayed surfaces for 60 seconds and remove excess from all surfaces with cotton pledgets.For tooth surfaces assigned to receive potassium iodide (KI), dispense 0.1 mL KI; using a new microbrush, dip the brush tip into the agent and apply to the decayed surface until precipitate forms. Then, reapply the agent until no precipitate forms, with 5- to 10-second intervals between reapplications.Place Orabase adhesive (Colgate Oral Pharmaceuticals, Inc) onto AgF-treated decayed surfaces, with or without KI.Advise participant to refrain from eating or drinking for 30 minutes after treatment.

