**For Creighton Dental AgF**
Remove food debris and plaque by brushing with a toothbrush (no toothpaste).Isolate teeth to be treated with cotton rolls and gauze and apply petroleum jelly to the gingiva and lips.Dry affected tooth surfaces and at-risk tooth surfaces to be treated with cotton pledgets.Dispense 0.05 mL AgF; bend the microbrush applicator and dip the tip of the applicator into the agent.Apply the agent with the microbrush onto the decayed surface and rub gently, maintaining contact with the tooth for 60 seconds. Apply the agent also to at-risk, nondecayed surfaces for 60 seconds and remove excess from all surfaces with cotton pledgets.Dispense 0.05 mL stannous fluoride. Using a new microbrush, dip the microbrush tip into the stannous fluoride solution and apply it to the decay-treated tooth surfaces.Place Orabase adhesive onto treated decayed surfaces.Advise participant to refrain from eating or drinking for 30 minutes after treatment.

Children allocated to the control group will be provided treatment by the oral health practitioner team (dental therapist and dental clinic assistant). Teeth to be restored using the ART approach will have the decayed tooth surfaces prepared using hand instruments only for caries removal without local anesthesia and teeth restored with a glass ionomer cement. Teeth restored using the HT will have the tooth surface cleaned, but caries will not be removed. The tooth will then be restored with a stainless-steel crown, cemented with a glass ionomer cement. The treating clinician will determine the type of restoration to provide for each control participant.

All the children will be reviewed at 12 and 24 months, and AgF treatments will be reapplied.

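### The second part of the primary outcome is defined on sound surfaces treated at baseline, a set with no comparable control-arm counterpart, and its DMFS measure can be altered by the control treatment itself

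*Protocol article*

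**What the plan says.** The Outcomes section gives the primary outcome two parts. The first is arrest of treated decayed teeth. The second, at issue here, is "the number of sound surfaces treated at baseline that became carious at follow-ups, measured by the count of decayed, missing, and filled tooth surfaces".

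Treatment of sound surfaces is described for the AgF arm only. Textbox 1 instructs the operator to "apply the agent also to at-risk, non-decayed surfaces for 60 seconds", and both AgF formulations carry this step. For the control arm, Intervention Description says of atraumatic restorative treatment (ART): "Teeth to be restored using the ART approach will have the decayed tooth surfaces prepared using hand instruments only". Of the Hall technique it says: "The tooth will then be restored with a stainless-steel crown, cemented with a glass ionomer cement". On the choice between them: "The treating clinician will determine the type of restoration to provide for each control participant".

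The prevention outcome is described differently elsewhere. The abstract's Methods speaks of "the proportion of surfaces at risk that decayed over the follow-up". Objective 2 is framed on the number of children who develop new active decay, judged against a noninferiority risk difference. Plans for Assessment and Collection of Outcomes lists decayed, missing, filled and arrested surfaces under ICDAS criteria and adds: "Treated teeth with intact, sound fillings will be assumed to have arrested decay".

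**The concern.** A randomized comparison needs the same set of units, defined the same way, in both arms. Here the set is defined by having been treated while sound, which is a feature of one arm's intervention. In that arm, membership is also decided after allocation. The abstract has an oral health practitioner prescribe the teeth for AgF, and Concealment Mechanism says the clinical team and treating clinicians know the assignment. Randomization does not protect a contrast between surfaces judged at risk in one arm and surfaces that happened to lie under a crown in the other.

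The measure adds a second problem. New caries and the DMFS count differ whenever a surface enters the filled category for a reason other than new caries on it. The control treatment can cause this; AgF application cannot.

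At stake is a primary outcome in a trial designed for noninferiority. An artefact in either direction could create or hide noninferiority with no true difference in prevention.

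**Working it through.** **No stated figure for this outcome.** The Sample Size section rests on arrest (61% against 81%). Its figures reproduce:

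- Two-sided α 0.05, 80% power, continuity correction: 90 per arm before clustering.
- With 15 clusters per arm and intracluster correlation 0.09: m = 90 × 0.91 / (15 − 90 × 0.09) = 81.9 / 6.9 = 11.87, rounded to 12, so 15 × 12 = 180 per arm.
- Attrition: 180 / 0.75² = 320 per arm.

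These figures have no bearing on the sound-surface outcome, for which the article states neither an incidence nor a margin.

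**Which surfaces enter the outcome, read literally.**

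| Surface at baseline | AgF arm | Control arm |
|---|---|---|
| Sound, judged at risk | Treated, so included | No treatment described, so not included |
| Sound, on a crowned molar | Not applicable as allocated treatment | Covered by the crown, arguably included |
| Sound, other | Not treated, not included | Not treated, not included |

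Eligibility Criteria admits children with or without caries. The article describes no control treatment of a caries-free child's sound surfaces, so such a child contributes nothing to this outcome in the control arm.

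**What the DMFS count does.** Under Recruitment, the baseline examination precedes treatment.

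- A decayed surface filled by ART moves from D to F. The DMFS change is 0, and the surface was never in the sound set.
- A sound surface under a crown can move from sound to F. The DMFS change is +1 without new caries.
- A sound surface treated with AgF stays sound unless it decays. The treatment itself adds 0.

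The artefact is therefore confined to sound surfaces covered by a crown or an extended restoration.

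**Illustration.** None of these inputs is in the document: 8 primary molars × 5 surfaces = 40; 3 decayed molars with 1 decayed surface each, leaving 37 sound; a true new-caries risk of 10% per sound surface in both arms; all baseline-sound surfaces as denominator; and a share h of decayed molars crowned. Sound surfaces under crowns = 3 × 4 × h = 12h.

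- Covered surfaces counted as F events: [12h + 0.10 × (37 − 12h)] / 37
- Covered surfaces kept in the denominator as not carious: [0.10 × (37 − 12h)] / 37
- Covered surfaces excluded: [0.10 × (37 − 12h)] / (37 − 12h) = 10%

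| Crown share h | AgF | Control, F events | Control, kept as not carious | Control, excluded |
|---|---|---|---|---|
| 0% | 10% | 10% | 10% | 10% |
| 10% | 10% | 4.78/37 = 12.9% | 3.58/37 = 9.7% | 10% |
| 25% | 10% | 6.40/37 = 17.3% | 3.40/37 = 9.2% | 10% |
| 50% | 10% | 9.10/37 = 24.6% | 3.10/37 = 8.4% | 10% |

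With 2 decayed surfaces per decayed molar, the 50% row becomes 21.9% (F events) and 8.7% (kept as not carious). The first coding favours AgF and the second favours control. Exclusion is neutral here only because risk is assumed equal on every sound surface. If sound surfaces on decayed molars carry higher risk, dropping them from one arm tilts the comparison too.

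**The case against.** A reader might infer that the trial will count control fillings and crowns as new caries, and so is biased toward AgF. The document does not support that. The event is a surface becoming carious. The assessment section lists decayed, missing, filled and arrested surfaces as separate categories and treats intact fillings as arrested decay. ART on a decayed surface leaves DMFS unchanged. The sign for crowned sound surfaces depends on a coding that the article does not state. The crown share is left to the clinician, so no size follows from the document, and with no crowns the crown artefact is zero. All of this stands.

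It can also be said that surface scoring of crowns belongs in an analysis plan or examiner manual not shown here, and that the abstract and Objective 2 already offer usable definitions. The first part is fair as to scoring detail, but it does not reach the denominator, which the Outcomes section states and which fits one arm only. The second part shows that a remedy is at hand, but it also means that three descriptions compete, and the one labelled primary is the one that cannot be compared between arms. The arrest rule for intact fillings concerns treated decay; it does not say whether a sound surface under a crown is at risk, an event or excluded.

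**Conclusion.** The concern holds in a limited form. As written, the second part of the primary outcome has no comparable set of surfaces in the control arm, and its DMFS measure does not match its event. The contrast can be biased in either direction. The assumed example, with 10% true risk in both arms, gives control rates of 12.9% to 24.6% under one coding and 9.7% to 8.4% under the other, for crown shares of 10% to 50%. These show that an unstated scoring rule can drive the result; they do not estimate this trial's bias. The lack of a comparable denominator rests on none of those assumptions. It follows from setting the Outcomes section beside the descriptions of the two interventions, and it should be corrected before recruitment, which is planned for March 2026.

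**What to change.** Define the outcome identically in both arms:

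- **Denominator:** all primary-molar surfaces recorded sound at the pre-treatment baseline examination, treated or not. This gives the abstract's surfaces at risk a definition that works in both arms.
- **Event:** new caries on that surface by ICDAS, or restoration or extraction for new caries after the baseline treatment visit. This replaces the total DMFS count.
- **Surfaces covered by the baseline crown or restoration:** not events. Report the result both with these surfaces kept in the denominator and with them excluded, since keeping them as non-events tilts toward control.
- **Sensitivity analysis:** molars wholly sound at baseline, acknowledging that this answers a narrower question.

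Reconcile the abstract, Objective 2, Outcomes and the assessment section to this definition, and say whether the primary analysis is per surface or per child.

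The cost is outcome wording, derivation code and some additional analyses. The surface-level ICDAS data are already planned, and neither treatment nor sample size changes. The remaining downside is that the estimate still depends somewhat on how crowned surfaces are handled; reporting both versions makes that dependence visible.
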